### 2.5. Psychological and Behavioral Measures

Students will complete questionnaires assessing motivation and behavioral determinants related to physical activity, screen time, sleep habits, and sedentary behaviors at baseline and at one-, three-, and six-month follow-up assessments. Prior to the main intervention study, the construct validity of translated and adapted questionnaires will be examined using data collected from an independent pilot sample of adolescents. Internal consistency of all multi-item scales will be assessed using Cronbach’s alpha coefficients. The primary outcomes will be changes in health-related behaviors, including physical activity, screen time, and sleep duration and quality, which represent the main targets of the FiTeens intervention. These outcomes will be assessed using both objective measures (accelerometers and Polar M400 smartwatch-based sleep assessment) and subjective questionnaire-based measures. Secondary outcomes will include psychological determinants of behavior based on Self-Determination Theory and the Theory of Planned Behavior, including motivation, behavioral intentions, attitudes, subjective norms, and perceived behavioral control related to physical activity, screen time, and sleep behaviors.

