## Abstract

(1) Background: Previous school-based interventions have addressed adolescent health behaviors such as physical activity, screen time, and sleep, but have predominantly targeted these behaviors independently rather than simultaneously. The Erasmus+ project FiTeens developed an integrated intervention combining theoretical content, videos, infographics, and interactive tasks to promote multiple health behaviors concurrently. The objective of the current article is to present the protocol for a school-based intervention study designed to examine the effects of the FiTeens program on adolescents’ physical activity, screen time, and sleep behaviors. We hypothesize that students receiving the FiTeens intervention will demonstrate increased physical activity, reduced screen time, and improved sleep outcomes compared with students in the control group. (2) Methods: Teachers will be introduced to the FiTeens tools prior to delivering the intervention to students in grades 5–9. Students will participate in an eight-week intervention program combining structured lessons and behavior-change challenges. Primary outcomes include changes in physical activity, screen time, and sleep duration and quality. Secondary outcomes include psychological determinants such as motivation and behavioral intentions. Data will be collected at baseline and at 1-, 3-, and 6-month follow-ups and analyzed using repeated measures ANOVA. (3) Expected results: The study will evaluate whether the intervention may contribute to improvements in health-related behaviors among adolescents, including increased physical activity, reduced screen time, and improved sleep outcomes. (4) Conclusions: The intervention based on FiTeens tools could have the potential to promote healthier lifestyle behaviors among students by increasing physical activity during leisure time, supporting the effective limitation of screen time and enhancing bedtime routines to improve sleep quality.

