### 2.2. Participants

Participants of this study will be students from grades 5 to 9 (ages 11–15) recruited from general education schools in Estonia, with one school designated as the intervention group and one school designated as the control group.

Sample size estimation was conducted using G*Power 3.1 based on a repeated measures ANOVA design with two groups and four measurement occasions. Assuming a medium effect size (f = 0.25), an alpha level of 0.05, and a statistical power of 0.80, a minimum sample size of 128 participants was required (64 participants per group). To account for potential participant attrition during follow-up assessments, the target sample size was increased by approximately 40–50%. Dropout rates of 20–40% have been reported in previous school-based interventions involving adolescents, which informed the decision to increase the sample size [14].

Participants in the control group will continue with their regular school curriculum and will not receive the FiTeens intervention during the study period.

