#### 2.5.4. Youth Leisure-Time Sedentary Behavior Questionnaire

The participants are asked to think back over the previous week and report the estimated average time devoted to each behavior during weekdays and weekend days, separately. The average time per day spent on each behavior and composite category was calculated as follows: [(weekday_time × 5) + (weekend_time × 2)]/7 [20]. Detailed information regarding the questionnaire items and response formats is presented in Appendix A (Table A1).

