#### 2.5.5. Leisure Time Exercise Questionnaire

Subjective leisure-time physical activity is assessed using the Leisure Time Exercise Questionnaire [21]. The instrument is designed to evaluate participation in vigorous physical activity during leisure time and provides an indicator of habitual physical activity behavior outside the school setting. Detailed information regarding the questionnaire items and response formats is presented in Appendix A (Table A1).

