#### 2.5.6. ActiGraph GT3X Accelerometer

Objective physical activity is assessed using ActiGraph GT3X accelerometers (ActiGraph LLC, Pensacola, FL, USA). The accelerometers are used to measure moderate-to-vigorous intensity leisure-time physical activity in adolescents. Accelerometer data will be processed using established criteria. A valid day will be defined as at least 10 h of wear time. Non-wear time will be identified as periods of at least 60 consecutive minutes of zero counts, allowing for short interruptions. Participants with at least 4 valid days, including at least one weekend day, will be included in the analysis. Missing data will be handled according to standard procedures, and only valid wear-time data will be included in the final analyses. Accelerometer data will be collected using a sampling epoch length of 15 s. Physical activity intensity will be classified using established cut-off points for adolescents (e.g., moderate-to-vigorous physical activity thresholds based on counts per minute). Data will be processed using appropriate software (e.g., ActiLife software, version 6.13.3, ActiGraph LLC). These criteria are consistent with commonly used protocols in adolescent physical activity research. Participants are instructed to wear the accelerometers on the hip for seven consecutive days in baseline, 1-month follow-up, 3-month follow-up and in 6-month follow-up.

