#### 2.5.7. Polar M400 Smartwatch

Objective sleeping duration is assessed using Polar M400 smartwatch (Polar Electro Oy, Kempele, Finland). The Polar M400 smartwatch is used to measure sleep duration in adolescents. Sleep duration will be assessed using the Polar M400 wrist-worn device. The device estimates sleep based on accelerometer-derived movement data, identifying periods of inactivity that correspond to sleep. Sleep duration is calculated automatically by the device as the time between sleep onset and wake-up, determined through changes in movement patterns and wrist activity levels. The extracted variable used in the analysis will be total nightly sleep duration (in hours), as recorded by the device. The Polar M400 smartwatch provides an estimate of sleep duration based on accelerometer-derived movement data and has been used as a practical tool for assessing sleep duration in free-living conditions. It should be noted that the device primarily estimates sleep duration rather than detailed sleep architecture or sleep quality. The Polar M400 smartwatch estimates sleep based on movement patterns and does not provide detailed information on sleep stages or sleep quality comparable to gold-standard methods such as polysomnography. Therefore, the objective sleep-related outcome in this study is limited to sleep duration. Participants are instructed to wear the device on the wrist for seven consecutive days at baseline, 1-month follow-up, 3-month follow-up, and 6-month follow-up.

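### Several objective and self-reported measures are equally primary, with no lead measure, deciding test or success rule, while the study is sized for one test at 0.05

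*Protocol article*

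**What the plan says.** Section 2.5 defines the primary set: "The primary outcomes will be changes in health-related behaviors, including physical activity, screen time, and sleep duration and quality". The Abstract gives the same unranked list: "Primary outcomes include changes in physical activity, screen time, and sleep duration and quality". Section 2.5 then says how these outcomes are measured: "These outcomes will be assessed using both objective measures (accelerometers and Polar M400 smartwatch-based sleep assessment) and subjective questionnaire-based measures". Devices and questionnaires are given equal standing.

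The sections that follow supply the measures:

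- **Activity, device (2.5.6):** "The accelerometers are used to measure moderate-to-vigorous intensity leisure-time physical activity in adolescents".
- **Activity, self-report (2.5.5):** "Subjective leisure-time physical activity is assessed using the Leisure Time Exercise Questionnaire".
- **Screen time, self-report (2.5.4):** "The average time per day spent on each behavior and composite category was calculated as follows". This is the only screen-time measure, and it may yield more than one variable.
- **Sleep duration, device (2.5.7):** "The extracted variable used in the analysis will be total nightly sleep duration (in hours), as recorded by the device". The same section limits the objective sleep outcome to duration.
- **Sleep habits, self-report (2.5.3):** the Sleep Hygiene Questionnaire. It is the only sleep-behaviour questionnaire described, so it is apparently the source for sleep quality, although the article does not say so.

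Section 2.4.1 also mentions a sleep diary, with no stated role in the analysis. Section 2.6 examines group, time and group x time effects for physical activity, screen time and sleep, and names none of them as decisive. Section 2.2 sizes the study with "an alpha level of 0.05, and a statistical power of 0.80", which is one alpha for one test.

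**The concern.** With equal standing and no rule, the protocol does not say in advance which result would show that the program worked. Two consequences follow.

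First, several measures each offer a chance of a significant result, and nothing in the protocol prevents one of them from being presented as the primary finding.

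Second, activity has both a device measure and a self-reported measure, with no statement of which leads if they differ. Students in the intervention school attend the lessons, set goals and discuss their challenges (Section 2.4.2), so they know they had the program. Their self-report is the measure most open to favourable bias. As written, a questionnaire gain with flat accelerometer data would still be a positive result on a primary outcome.

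**Working it through.** **Inputs.** Two groups, four occasions, f = 0.25, alpha 0.05, power 0.80, N = 128 (Section 2.2). Five measures, counted as listed above. Three assumptions are not in the document: each measure is tested at 0.05 (Section 2.6 states no level, so this is carried over from Section 2.2), any one significant result is claimed, and the measures have a common correlation r, which is varied.

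**1. The plan's own figure.** For two groups, d = 2f = 0.5. An exact two-sided t-test at 0.05 with 64 per group has power 0.801, so N = 128 is reproduced. It is reproduced as a single-occasion comparison, which equals a correlation of 1 between occasions. The figure covers one test of one variable.

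**2. False positives in either direction.** For five independent tests: 1 - 0.95^5 = 0.226. Simulated with correlated measures:

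| r | One contrast per measure | 3-df group x time test per measure |
|---|---|---|
| 0 | 22.6% | 22.7% |
| 0.2 | 21.9% | 22.0% |
| 0.3 | 20.9% | 21.2% |
| 0.5 | 18.3% | 18.8% |
| 0.7 | 14.9% | 15.5% |

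The range is about 15-23%, against 5% for a single test.

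**3. False positives in the program's favour.** A two-sided 0.05 test errs in one given direction 2.5% of the time. For one directional contrast on each of five independent measures: 1 - 0.975^5 = 0.119. By simulation, r = 0.2, 0.3, 0.5 and 0.7 give 11.1%, 10.5%, 9.1% and 7.5%. The range is about 7-12%, against 2.5%.

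**4. Power if the error rate is controlled.** The first Holm step over three measures uses 0.05/3 = 0.0167. Noncentral F with N = 128, f = 0.25:

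- Single-occasion two-group basis (noncentrality f²N = 0.0625 x 128 = 8): power 0.801 at 0.05 and 0.656 at 0.0167.
- Four-occasion between-groups test (noncentrality f²N x 4/(1 + 3r'), where r' is an assumed correlation between occasions): at 0.0167, power 0.87 for r' = 0.5 and 0.78 for r' = 0.7.
- Four-occasion group x time test (noncentrality f²N x 4/(1 - r')): above 0.99 at both correlations.

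If all five measures stayed primary under Bonferroni (0.05/5 = 0.01), the single-occasion power at 64 per group would be 0.59, and 0.80 would need 96 per group.

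**The case against.** The strongest reply has four parts.

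- **An analysis plan may hold the adjustment.** This is a condensed article, and a multiplicity procedure is commonly left to that plan. That is fair as far as the procedure goes. But the protocol itself gives device and questionnaire measures equal primary standing and sizes the study for one test. A later adjustment would not choose the lead measure, and it would leave the power statement at the wrong level.
- **Any-one-wins is not stated.** The hypothesis in the Abstract joins the three behaviours with an and. If all had to succeed, there would be no inflation. This stands as a condition on the figures. The protocol states neither an all-must-succeed rule nor an any-one rule, and that gap is the point.
- **The count of five is partly inferred.** The sleep hygiene questionnaire is not named as the sleep-quality measure. With four independent measures the either-direction figure would be 1 - 0.95^4 = 18.5%, so the conclusion does not depend on the fifth.
- **The two activity measures differ in content.** The questionnaire targets vigorous activity and the accelerometer moderate-to-vigorous activity, so differing results need not conflict. That is true, but it strengthens the case for saying which one decides.

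A reader might also infer an error rate of 29-40% by counting both the group and the group x time test on each measure. The document does not support this. The primary outcomes are changes, and the group main effect averages over baseline, so it does not test change. Nowhere is it said that a group main effect would be claimed as benefit.

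**Conclusion.** The concern holds in this form: several objective and self-reported measures are equally primary, nothing says which measure or test decides, and the study is sized for one test at 0.05. Under the assumptions of five measures, 0.05 each and any one significant result claimed, the chance of at least one false positive is about 15-23% in either direction and about 7-12% in the program's favour.

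A reader might conclude that the chance of a false claim for the program is 20% or more. That is not supported. The 22.6% figure counts results in both directions and assumes independence; the favourable share is about 12% at most, and correlation lowers both. Nor should 0.66 be read as the power of the planned four-occasion analysis. It belongs to the single-occasion comparison that reproduces N = 128. The change should be made, but it does not invalidate the study.

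**What to change.** 1. Name one primary measure per behaviour: accelerometer moderate-to-vigorous activity, the questionnaire screen-time composite (self-report, as no other screen-time measure exists), and watch sleep duration.
2. Name one deciding test of change: the group x time interaction, or the baseline-to-1-month contrast, since Section 3 already places the expected effect at one month.
3. Apply Holm across the three at an overall 0.05.
4. Move the exercise questionnaire and the sleep hygiene score to secondary. State openly that sleep quality, now a declared primary outcome in the Abstract and Section 2.5, becomes secondary because the watch measures only duration (Section 2.5.7).
5. Restate power in Section 2.2 for the chosen test at the first Holm step, with the assumed correlation between occasions. On the single-occasion basis it is about 0.66. For the four-occasion model it is higher, by an amount that depends on that correlation.

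The cost is lower stated power and a demoted sleep-quality outcome, which is a change to the primary outcomes and more than an edit of wording. No new data are needed. Holm controls only the testing of several measures; it does nothing about school differences that cannot be separated from the program with one school per arm (Section 2.1).

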#### 2.5.1. Motivation Assessment

Motivation will be assessed using the Motivation to Limit Screen-time Questionnaire (MLSQ) [15] and a validated physical activity motivation questionnaire based on Self-Determination Theory [16]. The MLSQ will be used to assess motivation related to screen time and, in an adapted form, sleep-related behaviors. The physical activity motivation questionnaire assesses autonomous motivation (intrinsic motivation and identified regulation) and controlled motivation (introjected and external regulation) toward leisure-time physical activity. Together, these instruments assess autonomous motivation, controlled motivation, and amotivation across the three target health behaviors. The adapted sleep-related version of the MLSQ will retain the original theoretical structure of the instrument. Construct validity and internal consistency of the adapted measures will be evaluated prior to the main study. Detailed information regarding questionnaire items and response for mats is presented in Appendix A (Table A1).

#### 2.5.2. Behavioral Determinants Assessment

Behavioral determinants will be assessed using a questionnaire based on the Theory of Planned Behavior. The questionnaire measures attitudes, subjective norms, perceived behavioral control, and intentions related to physical activity, screen time, and sleep. Responses are recorded using seven-point Likert-type scales. Higher scores indicate stronger endorsement of the respective construct [17,18]. Detailed information regarding the questionnaire items and response formats is presented in Appendix A (Table A1).

#### 2.5.3. Sleep Hygiene Questionnaire

The questionnaire is aimed at children/adolescents between 6 and 17 years of age. The questionnaire evaluates sleep-related behaviors and habits during the previous two weeks, including bedtime routines, caffeine consumption, screen use before bedtime, and other behaviors known to influence sleep quality and duration. Participants respond to items reflecting the frequency of specific behaviors, providing an overall indication of sleep hygiene practices [19]. Detailed information regarding the questionnaire items and response formats is presented in Appendix A (Table A1).

#### 2.5.4. Youth Leisure-Time Sedentary Behavior Questionnaire

The participants are asked to think back over the previous week and report the estimated average time devoted to each behavior during weekdays and weekend days, separately. The average time per day spent on each behavior and composite category was calculated as follows: [(weekday_time × 5) + (weekend_time × 2)]/7 [20]. Detailed information regarding the questionnaire items and response formats is presented in Appendix A (Table A1).

#### 2.5.5. Leisure Time Exercise Questionnaire

Subjective leisure-time physical activity is assessed using the Leisure Time Exercise Questionnaire [21]. The instrument is designed to evaluate participation in vigorous physical activity during leisure time and provides an indicator of habitual physical activity behavior outside the school setting. Detailed information regarding the questionnaire items and response formats is presented in Appendix A (Table A1).

#### 2.5.6. ActiGraph GT3X Accelerometer

Objective physical activity is assessed using ActiGraph GT3X accelerometers (ActiGraph LLC, Pensacola, FL, USA). The accelerometers are used to measure moderate-to-vigorous intensity leisure-time physical activity in adolescents. Accelerometer data will be processed using established criteria. A valid day will be defined as at least 10 h of wear time. Non-wear time will be identified as periods of at least 60 consecutive minutes of zero counts, allowing for short interruptions. Participants with at least 4 valid days, including at least one weekend day, will be included in the analysis. Missing data will be handled according to standard procedures, and only valid wear-time data will be included in the final analyses. Accelerometer data will be collected using a sampling epoch length of 15 s. Physical activity intensity will be classified using established cut-off points for adolescents (e.g., moderate-to-vigorous physical activity thresholds based on counts per minute). Data will be processed using appropriate software (e.g., ActiLife software, version 6.13.3, ActiGraph LLC). These criteria are consistent with commonly used protocols in adolescent physical activity research. Participants are instructed to wear the accelerometers on the hip for seven consecutive days in baseline, 1-month follow-up, 3-month follow-up and in 6-month follow-up.

#### 2.5.7. Polar M400 Smartwatch

Objective sleeping duration is assessed using Polar M400 smartwatch (Polar Electro Oy, Kempele, Finland). The Polar M400 smartwatch is used to measure sleep duration in adolescents. Sleep duration will be assessed using the Polar M400 wrist-worn device. The device estimates sleep based on accelerometer-derived movement data, identifying periods of inactivity that correspond to sleep. Sleep duration is calculated automatically by the device as the time between sleep onset and wake-up, determined through changes in movement patterns and wrist activity levels. The extracted variable used in the analysis will be total nightly sleep duration (in hours), as recorded by the device. The Polar M400 smartwatch provides an estimate of sleep duration based on accelerometer-derived movement data and has been used as a practical tool for assessing sleep duration in free-living conditions. It should be noted that the device primarily estimates sleep duration rather than detailed sleep architecture or sleep quality. The Polar M400 smartwatch estimates sleep based on movement patterns and does not provide detailed information on sleep stages or sleep quality comparable to gold-standard methods such as polysomnography. Therefore, the objective sleep-related outcome in this study is limited to sleep duration. Participants are instructed to wear the device on the wrist for seven consecutive days at baseline, 1-month follow-up, 3-month follow-up, and 6-month follow-up.

### 2.6. Statistical Analysis

All statistical analyses will be conducted using IBM SPSS Statistics for Windows, Version 29.0 (IBM Corp., Armonk, NY, USA) and JASP, Version 0.17.1 (JASP Team, Amsterdam, The Netherlands). Descriptive statistics will be calculated for all study variables. The primary statistical analysis will be performed using repeated measures ANOVA, which was selected because it is appropriate for evaluating within-subject changes across repeated measurement occasions and between-group differences over time in the present study. The analysis will examine the main effects of group and time, as well as the group × time interaction effect for physical activity, screen time, and sleep-related outcomes across four measurement points (baseline, 1-, 3-, and 6-month follow-up assessments). Baseline measurements will be included in the repeated measures design to evaluate changes over time within and between groups. Independent samples *t*-tests will additionally be used to examine baseline differences between the intervention and control group, as well as differences between study completers and dropouts at baseline. As schools are allocated to intervention and control conditions at the school level, baseline differences between groups will be examined prior to the main analyses and considered when interpreting the findings. Potential school-level effects and residual confounding cannot be completely excluded and should therefore be considered when interpreting the study findings. Prior to the main analyses, data will be screened for missing values, and the extent and pattern of missingness will be examined and reported. Missing data will be addressed using multiple imputation procedures prior to analysis. An intention-to-treat approach will be applied, including all participants as originally allocated to their groups. Dropout rates and reasons for attrition will be reported and examined. Potential confounding variables, such as age and gender, will be considered where appropriate.

